### Delivering the intervention

All participants will undergo 10 online therapy sessions (once-weekly) with each session lasting for 40-60 minutes. They will be divided into four small groups, each comprising five participants and a therapist. Before each session, the therapy module will be given as an online self-learning source via videos in a website specifically developed for this training. The videos will divide the module content into several parts with each video lasting about 10 minutes. To confirm the participants have watched the videos, there will be a post-test measurement with no passing mark as the purpose is to assert the important points contained in the videos. The participants will then be encouraged to discuss things they understand or do not understand from their online self- learning sessions during each therapy session. There will also be several tasks that must be completed by the participants and then discussed with the therapist during each therapy session (e.g., ‘please identify the urges you feel over the next week’). To evaluate acceptability, participants will complete a satisfaction questionnaire after each therapy session. The questionnaire will use a five-point Likert scale, ranging from “very unsatisfied” to “very satisfied,” to measure their level of satisfaction with the iCBT sessions. Researchers from Flinders Centre for Gambling Research and Universitas Indonesia will meet online every two weeks to discuss participants and to provide input on treatment.

### Providers of iCBT

Two psychiatrists with expertise in GD from Department of Psychiatry, Faculty of Medicine, Universitas Indonesia will facilitate each group session in this study. The roles of the therapist are to: (1) lead and moderate iCBT sessions based on (but not limited to) the module, (2) establish a safe and warm environment, (3) provide consultation, including out-of-session, and (4) contact absent participants to encourage attendance.

### Participant characteristics

The following descriptive data will be obtained via a self-administered questionnaire: age, gender, education level, ethnicity, religion, approximate residential location, marital status, employment status, monthly income, last gambling session, age during first instance of gambling, frequency of gambling in a month, first person to introduce gambling, other people around the patient who also have gambling problems, media used to gamble, types of device used, types of gambling played, average duration of gambling during weekday and weekend, lowest and highest bet ever placed, total money lost to gambling, purpose of gambling, negative impacts from gambling, help seeking behaviors, substance use history, usage of substance during gambling session, and (if ever) rehabilitation due to substance use history.

### Sample size

The sample size for this study was determined using the formula for matched samples continuous outcome: n = ((Z
_α_ + Z
_β_) × S/E)
^2^, where Z
_α_ is the value from the standard normal distribution reflecting the confidence level that will be used (Z
_α_ = 1.96 for 95%), power is determined to be 80% (Z
_β_ = 0.84). S is the standard deviation score using GUS as primary outcome, which is 11 from a previous study.
^
31
^ Margin of error was determined to be 5 units. The sample size needed using the above formula is 19.36 samples, which is then rounded to 20 samples to accommodate the group therapy sessions.

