					T1	T2	T3
Gambling symptom severity	G-SAS	Sum of 12 items	Continuous, 8 (mild) to 48 (extreme)	Lower	v	v	v
Gambling urges	GUS	Sum of 6 items	Continuous, 0 to 42, the higher the score indicating the higher the urges/craving	Lower	v	v	v
Gambling- related cognitive distortions	GRCS	5 domains, with the highest percentage being the most dominant domain.	Continuous, 0% to 100% per domain	Lower	v	v	v
Impulsivity	BIS_11	Sum of 30 items	Continuous, 30 to 120, the higher the score indicating the higher levels of impulsivity	Lower	v	v	v
Readiness to change	URICA	Means of each stage of change score	Continuous, means of 9.3 (pre-contemplation), 11 (contemplation) and 12.6 (participation)	Lower	v	v	v
Nonspecific psychological distress	SRQ-20	Sum of 20 items	Continuous, 0 to 20, with scores >5 indicating mental distress	Lower	v	v	v
Quality of life	WHOQOL- BREF	4 domains, with transformed score used	Continuous, 0 to 100 per domain, the higher the score the higher the quality of life	Higher	v	v	v

G-SAS, Gambling Symptom Assessment Scale; PGSI, Problem Gambling Severity Index; GUS, Gambling Urge Scale; GRCS, Gambling Related Cognitions Scale.

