### Statistical analysis

Evaluation of the response to CBT will be measured using mixed model analyses. Statistical analysis will be carried out using the Statistical Package for the Social Sciences (SPSS) software version 25.0. The raw data obtained in this study only be accessible to the authors. Missing data will be handled on whether they are at random.

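### The matched-samples calculation does not identify S = 11 as the SD of the within-person GUS change and states no pre-post correlation, so the required size and 80% power are unsupported for the paired comparison

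*Protocol article*

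**What the plan says.** The Sample size section of the protocol article names its method: "The sample size for this study was determined using the formula for matched samples continuous outcome". The formula printed there is n = ((Zα + Zβ) × S/E)², with Zα = 1.96 and Zβ = 0.84 for 80% power. On S it says: "S is the standard deviation score using GUS as primary outcome, which is 11 from a previous study". On E it says: "Margin of error was determined to be 5 units". The result is given as: "The sample size needed using the above formula is 19.36 samples, which is then rounded to 20 samples".

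The section mentions neither a change nor a difference score when it introduces S, and it gives no correlation between the repeated measurements. Table 1 gives the range of the Gambling Urge Scale (GUS) as 0 to 42, assessed at T1, T2 and T3. The Statistical analysis section plans mixed models.

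**The concern.** With matched samples, the quantity tested is the mean within-person difference, and its standard error depends on the SD of that difference. An SD of GUS scores at one time point is a different quantity. The two are linked by the pre-post correlation, which the protocol does not give. The wording reads most naturally as a score SD.

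What is at stake is whether the stated size and power say anything about the T1-T2 comparison. The printed 19.36 also does not follow from the printed inputs, which is a separate defect. Correcting that multiplication alone would give 38, and 38 belongs to the paired comparison only if the SD of change is in fact 11. The study is also meant to inform a later conclusive trial, which will need the SD of change and the correlation for its own planning.

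**Working it through.** **Inputs from the Sample size section:** Zα = 1.96, Zβ = 0.84, S = 11, E = 5 GUS units, stated result 19.36, planned n = 20. **Not in the document:** the T1-T2 correlation r. It is assumed below to be 0.3, 0.5 or 0.7.

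**Step 1. The plan's own figure.** ((1.96 + 0.84) × 11/5)² = 6.16² = 37.95, which rounds up to 38. The printed 19.36 is not reproduced. It equals 4.4², which arises if E = 7 (2.8 × 11/7 = 4.4) or if the sum of the Z values is 2.0 (2.0 × 11/5 = 4.4). The document does not show which of these, if either, happened. This is the separate arithmetic error.

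**Step 2. From score SD to SD of change.** In general, SD of change = √(SD₁² + SD₂² − 2r·SD₁·SD₂). If the T1 and T2 SDs are both 11, this becomes 11 × √(2(1 − r)):
- r = 0.3: 11 × √1.4 = 13.0
- r = 0.5: 11 × √1.0 = 11.0
- r = 0.7: 11 × √0.6 = 8.5

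**Step 3. The plan's formula with the SD of change.** n = (2.8 × SD of change / 5)², using unrounded SDs. Power is for 20 participants and 5 units, paired t test, two-sided 5%, 19 degrees of freedom. Detectable change is at 80% power, where the noncentral t distribution gives 0.660 × SD of change. The 95% confidence interval (CI) half-width is 2.093 × SD of change / √20.

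| r (assumed) | SD of change | Formula n | Power at n = 20 | Detectable change | CI half-width |
|---|---|---|---|---|---|
| 0.3 | 13.0 | 53.1, so 54 | 37% | 8.6 | 6.1 |
| 0.5 | 11.0 | 37.9, so 38 | 49% | 7.3 | 5.1 |
| 0.7 | 8.5 | 22.8, so 23 | 70% | 5.6 | 4.0 |

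**Step 4. What 80% power with 20 participants would require.**
- Normal formula: SD of change = 5 × √20 / 2.8 = 7.99, so r = 1 − 7.99²/242 = 0.74.
- Paired t test: SD of change = 5/0.660 = 7.57, so r = 1 − 7.57²/242 = 0.76.

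**Step 5. If 11 is already the SD of change.** The r = 0.5 row applies: n = 38 and about 49% power. That gap is due entirely to the arithmetic in Step 1.

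**The case against.** **The wording is loose and the source is not at hand.** A reader might infer that the protocol definitely used a score SD in place of a change SD. The document does not support that. Its phrase does not exclude a change SD, it stands beside a formula correctly named for matched samples, and the cited study is not available. What stands is that S is not identified as the SD of change.

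**The direction is unknown.** A reader might also infer that this input makes the study too small. It need not. Under equal SDs, S = 11 is exactly right at r = 0.5, overstates the required n above 0.5 and understates it below. The effect of this input alone is the movement from 38 to 54 or to 23. The drop from 80% to about 49% in the r = 0.5 row belongs to the arithmetic error. This objection stands in full.

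**The conversion assumes equal SDs.** After treatment, on a scale bounded at 0, the T2 SD may differ. As an illustration, with SDs of 11 and 8 the SD of change is 11 at r = 64/176 = 0.36, not 0.5. This stands, so the assumption has to be stated.

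**It is a pilot with 20 participants, analysed by mixed models.** The number recruited need not change, and paired-t power for T1-T2 is only a proxy for the planned analysis. Both are fair and limit the practical weight. They do not rescue the power claim, because the article chose to print a powered calculation and to describe S itself. This is therefore not a detail left to a fuller document.

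**Conclusion.** The point holds in a limited form. S = 11 is described in words that fit a score SD, is not identified as the SD of the T1-T2 change, and comes without a correlation. The required size and the 80% power are therefore unsupported for the paired comparison.

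On the score-SD reading, with equal SDs and r assumed between 0.3 and 0.7, 20 participants have about 37% to 70% power for 5 units. They reach 80% only if r is about 0.75 or higher. On the change-SD reading, power is about 49%. So neither reading of 11 yields the stated 80% with 20 participants unless the correlation is that high, and the protocol gives no basis for assuming so. Which reading is right, and in which direction a score SD would mislead, cannot be settled from the document.

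**What to change.** Revise the Sample size paragraph once, together with the arithmetic correction:

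1. State whether 11 is the SD of the T1-T2 change or the SD of a GUS score.
2. If it is a score SD, convert it with a stated r over a range such as 0.3, 0.5 and 0.7, and state the equal-variance assumption.
3. Keep the 20 participants, and replace the 80% power claim with what they deliver, as either the detectable change or the 95% CI half-width in the Step 3 table. If 11 is the SD of change, the r = 0.5 row is the one to report.
4. Commit to reporting the observed SD of change and r from this pilot as planning inputs for the later trial.

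The cost is one reworded paragraph and the loss of the 80% figure. No participants, visits or measurements are added.

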**Methods:**

This non-randomized pilot and feasibility study will recruit 20 people with GD. All participants will receive the iCBT intervention through self-learning videos and guided weekly group sessions. The effectiveness of the intervention will be assessed at baseline (week 0), post- treatment completion (week 10), and 6 weeks post-treatment (week 16). The outcomes measured will be the change in gambling symptoms, gambling urges, cognitive distortions, readiness to change, emotional problems, and quality of life of the participants.

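### The printed sample-size formula and inputs give 38, not 19.36, so the inputs, the result and the 80% power claim cannot all be right

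*Protocol article*

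**What the plan says.** The calculation is in the Sample size section of the protocol article. It opens: "The sample size for this study was determined using the formula for matched samples continuous outcome". The formula printed is n = ((Zα + Zβ) × S/E)².

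The inputs are all given in the same paragraph:
- Zα = 1.96, for 95% confidence.
- Zβ = 0.84, since "power is determined to be 80" per cent.
- S = 11: "S is the standard deviation score using GUS as primary outcome, which is 11 from a previous study".
- E = 5: "Margin of error was determined to be 5 units".

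The result is reported as "The sample size needed using the above formula is 19.36 samples, which is then rounded to 20 samples".

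The design is a single group. The abstract says: "All participants will receive the iCBT intervention through self-learning videos and guided weekly group sessions". A one-sample or paired formula is therefore the right type for a before-after change.

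**The concern.** This calculation is the only basis the article gives for the number of participants, and its answer does not follow from its own inputs. It is not a detail left to a fuller document: formula, inputs and result are all printed, and they disagree.

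Although this is a pilot and feasibility study, effectiveness is one of its stated aims and the GUS is one of the primary outcomes. A reader of the results may therefore weigh a GUS change, or the lack of one, against the stated 80% power for 5 units. If 5 units was the intended difference, that power is not there. The study is also meant to inform a later conclusive trial, whose planners could reuse this paragraph.

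Two features of the wording make the paragraph harder to interpret. E is called a margin of error, which is the language of precision, yet the formula contains Zβ, so E acts as a detectable difference. And S is not clearly identified as the SD of the within-person change, which is what a matched-samples formula needs.

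**Working it through.** **Inputs**, all from the Sample size section: Zα = 1.96, Zβ = 0.84, S = 11, E = 5, stated result 19.36, planned n = 20.

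**1. The plan's own formula with its own inputs.**
n = ((1.96 + 0.84) × 11/5)² = (2.80 × 2.2)² = 6.16² = 37.95, so 38. The stated 19.36 is not reproduced. Unrounded normal quantiles give 37.99, so rounding is not the cause. A one-sided 5% test gives 29.9, so sidedness is not the cause either. A paired t-test needs 40 for 80% power.

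**2. What does return 19.36.** Since √19.36 = 4.4, the product (multiplier × 11/E) must equal 4.4.
- Full multiplier 2.80 with E = 7: (2.80 × 11/7)² = 4.4² = 19.36.
- Multiplier 2 with E = 5: (2 × 11/5)² = 4.4² = 19.36. This is a precision-type calculation with no power term.
- Multiplier 1.96 with E = 5: (1.96 × 11/5)² = 18.59, which is not 19.36. The second route therefore needs 2 in place of the printed 1.96.

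**3. Power at n = 20 if E = 5 and 11 is the SD of the paired change** (two-sided 5%).
- Normal: Φ(5 × √20/11 − 1.96) = Φ(2.033 − 1.96) = Φ(0.073) = 52.9%.
- Paired t (noncentral t, 19 df): 48.8%.

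**4. Change detectable with 80% power at n = 20, SD of change 11.**
- Normal: 2.80 × 11/√20 = 6.89 units.
- Paired t: 7.26 units.

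**5. Power at n = 20 if E = 7, SD of change 11.**
- Normal: Φ(7 × √20/11 − 1.96) = Φ(2.846 − 1.96) = Φ(0.886) = 81%.
- Paired t: 77%.

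**6. Precision at n = 20, SD of change 11.** 95% CI half-width = 2.093 × 11/√20 = 5.15 units.

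**7. If 11 is instead the SD of a single score.** The SD of change is 11 × √(2(1 − ρ)). The article gives no pre-post correlation ρ, so the values below are assumptions. Power is for a 5-unit change at n = 20.

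| Assumed ρ | SD of change | n from the plan's formula | Power (paired t) |
|---|---|---|---|
| 0.3 | 13.0 | 53.1 | 37% |
| 0.5 | 11.0 | 37.9 | 49% |
| 0.7 | 8.5 | 22.8 | 70% |

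A correlation of about 0.76 would be needed for 80% power by the paired t-test.

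**The case against.** The strongest objection is that the slip may lie in one printed digit and not in the power claim. Keeping every stated constant and changing only E from 5 to 7 reproduces 19.36 exactly. In that case 20 participants do have about 80% power by the plan's own method, and only the printed margin is wrong. This stands. It is why the low power figure has to be conditional on E = 5.

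A reader might infer that 19.36 must be a precision calculation passed off as a power calculation, particularly given the margin-of-error wording. The article does not support that as a fact. It requires a Z of 2, which appears nowhere in the text, and the E = 7 reading fits at least as well. It would be equally unsafe to conclude outright that the study has half the power it claims, or that the 80% statement must be removed whatever the intended E.

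Three further points limit the size of the problem. The description of S is ambiguous, so about 50% is not a fixed figure even with E = 5. The power figures are for a single paired comparison, whereas the Statistical analysis section plans mixed models over three time points, so they only approximate the planned analysis. And in a 20-person feasibility study the consequences for interpretation are possible rather than certain.

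A reader might also add the lack of an allowance for loss to follow-up. The article gives no expected loss and plans mixed models, which can retain partly observed participants, so that is not part of this point.

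None of this removes the contradiction: on any reading, at least one printed element of the paragraph is wrong.

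**Conclusion.** The paragraph is wrong as written. Its formula and inputs give 38, about twice the stated 19.36, and the inputs, the result and the 80% power cannot all hold. That conclusion needs no assumption.

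The cause cannot be settled from the article, and the consequence depends on it:
- If E = 5 and 11 is the SD of the paired change, the planned 20 have 53% power (normal) or 49% (paired t) for 5 units. They reach 80% only for about 7 units.
- If E was meant to be 7, the planned 20 are adequate by the plan's formula (81%) and slightly short by the paired t-test (77%). The error is then the printed margin.
- If 11 is the SD of a single score, power for 5 units depends on a correlation the article does not give. It runs from 37% to 70% for assumed values of 0.3 to 0.7.

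This must be corrected, because it is the only stated basis for the sample size. It does not call for more participants.

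**What to change.** Keep 20 participants and reconcile the paragraph. The sponsor should establish from its own records which of E, the multiplier or the result was misprinted or miscalculated.

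- **If E = 5 stands:** state that the formula gives 38. Replace the 80% power claim with about 50% for a 5-unit change and about 80% for a 7-unit change. Justify 20 on feasibility and on precision, with an expected 95% CI half-width of about 5.15 GUS units.
- **If E was meant to be 7:** correct the printed margin to 7 and keep the power statement, giving 81% by the normal formula and 77% by the paired t-test.
- **In either case:** call E a detectable difference rather than a margin of error, and say whether 11 is the SD of the score or of the within-person change. If it is the SD of the score, show power over a stated range of correlations.

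The cost is rewording one paragraph. The article's Study status section says recruitment had not begun at submission. The only downside is that the stated power or the detectable difference becomes less favourable.

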### Statistical analysis

Evaluation of the response to CBT will be measured using mixed model analyses. Statistical analysis will be carried out using the Statistical Package for the Social Sciences (SPSS) software version 25.0. The raw data obtained in this study only be accessible to the authors. Missing data will be handled on whether they are at random.

### Data monitoring

Data on adverse events, including hospitalization, arrest, and death, will be collected from the participants’ contact person, treating physician or medical staff. In addition, participants will be interviewed at T2 to determine whether they have experienced any subjective harmful effects (e.g., withdrawal syndrome, increased cravings) after joining this program.

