^ Similar findings also come from an Indonesian study that indicated only 15.5% of people seek treatment for GD.
^
2
^ Problem gambling and its consequences can remain hidden within families, usually over extended periods, and help-seeking is often the last resort after significant adverse events or crises such as family breakdown, loss of employment, legal issues, or deterioration of mental health.
^
13
^
^,^
^
14
^ Since delivering treatment for gambling disorders is challenging in Indonesia due to its vast and varied territory, iCBT appears to be a promising treatment option. However, research regarding the effectiveness of iCBT is still very scarce in Indonesia. This pilot study aims to examine the effectiveness, acceptability and feasibility of iCBT for GD in Indonesia.

PROTOCOL

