### Participants and settings

A total of 20 participants screened as probable pathological gambler (indicating severe and pervasive problem gambling) based on South Oaks Gambling Screen (SOGS) will be recruited using online advertisements via social media and through consecutive sampling by directly approaching current and former patients in inpatient and outpatient services in Cipto Mangunkusumo Hospital, Indonesia. All participants will be allowed to continue their prior treatment as indicated.

The inclusion criteria include age between 18-59 years old, fluent in Bahasa Indonesia, be diagnosed as person with GD using ICD-11 by medical doctors at [name] General Hospital, Jakarta, Indonesia. Exclusion criteria are no history of gambling in the past six months, history of severe psychiatric disorder (i.e., psychotic disorders, severe mood disorders, and intellectual disability), history of neuropsychiatric disorders (e.g., seizures), and inability to access web browsers and online conferencing platforms. There will be no drop out criteria in this study. Adherence to the treatment will be evaluated to optimize the configuration of the iCBT for future studies.

The South Oaks Gambling Screen is chosen as a screening tool because of its widespread use internationally.
^
16
^ The adaptation to Indonesian version in community setting yielded a good validity and reliability testing, indicating SOGS as a good instrument to screen for GD in Indonesia.
^
2
^

Following the determination of a participant’s eligibility, several instruments will be employed to assess the effectiveness of the study. The primary outcomes will be evaluated using the Indonesian version of the Gambling Symptom Assessment Scale (G-SAS) to measure gambling symptoms, the Gambling Urge Scale (GUS) to assess gambling urges, and the Gambling Related Cognitions Scale (GRCS) to evaluate cognitive distortions. Secondary outcomes will be measured using the Barratt Impulsiveness Scale-11 (BIS-11) to assess impulsivity, the University of Rhode Island Change Assessment Scale (URICA) to gauge readiness to change, the World Health Organization Quality-of-Life Scale (WHOQOL-BREF) to evaluate quality of life, and the Self Rating Questionnaire-20 (SRQ-20) to assess emotional problems.
^
17
^
^–^
^
27
^ The assessment schedule is presented in
Table 1 and
Figure 2.

**Table 1. T1:** Outcome and measurement.

Outcome	Measurement	Data for analysis	Type and score range	Hypothesis	Assessment time point		

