## Discussion

The aim of our study is to evaluate the effectiveness, acceptability and feasibility of an online CBT intervention for patients with GD in Indonesia. Previous studies found that only few of those with gambling problems seek professional help.
^
2
^
^,^
^
5
^
^,^
^
23
^ Multidimensional factors including social, cultural, and personal could be contributing to their reluctance to seek treatment. There are a number of obstacles that inhibit help-seeking such as pressure from others to continue gambling, the desire to handle the issues on their own, stigma, secrecy, shame, not admitting problems, practical concerns (such as lack of availability and cost of treatment), worries about treatment, uncertainty, and avoidance.
^
32
^
^–^
^
34
^ Gambling is strictly prohibited under the Indonesian Criminal Code and engaging in such activities is punishable by law.
^
35
^ Although there is currently no research on the subject, it is possible that the illegality of GD is one of the contributing factors to the low rate of help-seeking in GD. Internet-based therapies have the potential to address these barriers by minimizing the stigma associated with seeking treatment, as participants are not required to attend a physical therapy site. Additionally, they help to overcome practical challenges, such as travel time to treatment facilities and scheduling conflicts with other obligations, including childcare and paid work. Furthermore, these therapies can be tailored to meet cultural and language needs to geographically challenging areas, enhancing their acceptability among the target population.
^
36
^ Group CBT model is selected because it is not inferior to individual CBT in terms of efficacy, while being more resource-efficient.
^
37
^
^,^
^
38
^ This approach allows for the treatment of a larger number of individuals with GD, particularly in resource-limited settings, such as those found in LMICs especially Indonesia, where participants are spread across multiple islands. However, maintaining the confidentiality of personal information among participants must be prioritized throughout the therapy sessions.

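### The sources named for hospitalization, arrest and death are all third parties, and no harms inquiry is stated at week 16, so these events may be under-ascertained

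*Protocol article*

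**What the plan says.** Under Data monitoring, the protocol article splits harms into two channels.

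- **Objective serious events.** Data on hospitalization, arrest and death are to come from the participant's "contact person, treating physician or medical staff".
- **Subjective effects.** In addition, "participants will be interviewed at T2 to determine whether they have experienced any subjective harmful effects". The examples given are withdrawal and stronger craving.

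No inquiry about harms is stated at T3. Table 1 lists only the outcome scales at that visit.

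Other sections bear on how well these channels would work:

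- Under Participants and settings, people "will be recruited using online advertisements via social media and through consecutive sampling" of current and former hospital patients. Everyone must "be diagnosed as person with GD using ICD-11 by medical doctors at" a named general hospital in Jakarta. The listed criteria mention neither a contact person nor a continuing treating physician. Earlier care may go on but is not required: "All participants will be allowed to continue their prior treatment as indicated". There are no drop-out criteria.
- Under Providers of iCBT, psychiatrists facilitate the group sessions and contact people who miss them. The stated purpose of that contact is attendance.
- The Introduction says "Problem gambling and its consequences can remain hidden within families, usually over extended periods". The Discussion says "Gambling is strictly prohibited under the Indonesian Criminal Code and engaging in such activities is punishable by law".

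**The concern.** The person best placed to report an arrest or an admission is the participant, and the participant is not among the sources named for either. Hospital staff and treating physicians have no routine way to learn of an arrest, and may not hear of an admission elsewhere. A contact person may know, if there is one and that person is asked.

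Arrest is no remote possibility here, since the article itself notes that gambling is a criminal offence in Indonesia.

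Two things are at stake. First, a feasibility study should give a usable first account of harms, and with 20 participants one unrecorded event is 1/20 = 5% of the sample. Second, the Statistical analysis section makes the treatment of missing data depend on whether they are missing at random. If an arrest or admission lies behind a missed assessment and is never recorded, that judgement loses the evidence it most needs.

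**Working it through.** The article gives no figure for event rates or for the number of participants without an informant, so there is none to reproduce. The check is mainly textual.

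**1. Who could report each event, under the sources as named?**

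| Event | Contact person | Treating physician or medical staff | Participant |
|---|---|---|---|
| Death | Yes, if one is named | If informed | Not possible |
| Hospitalization | Yes, if one is named | At their own hospital; elsewhere only if told | Not a named source |
| Arrest | Yes, if one is named and aware | Only if told | Not a named source |
| Subjective effects | Not stated | Not stated | Once, at T2 |

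Third parties are the right source for death. For the two events that a living participant could report, the direct route is not stated.

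**2. When is there contact with the participant?** The Abstract puts the assessments at weeks 0, 10 and 16.

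- Weeks 0 to 10: weekly sessions for those who attend, and a call from the therapist for those who do not. Either could bring an event to light, but neither is described as a harms inquiry.
- Week 10 (T2): one harms interview, limited to subjective effects.
- Weeks 10 to 16: no session and no harms inquiry stated. This is 16 − 10 = 6 weeks, or 6/16 = 37.5% of follow-up.
- Week 16 (T3): scales only.

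**3. Who is most exposed?** Non-attenders stay in the study because there are no drop-out criteria. They lose the weekly session as an informal route and depend most on third parties.

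**4. Sensitivity, on assumptions only.** Suppose that *u* of the 20 participants have no informant who learns of an event, and that each has event risk *p* over the study. The chance of at least one event among them is 1 − (1 − p)^u.

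| u of 20 | p = 2% | p = 5% | p = 10% |
|---|---|---|---|
| 2 | 4% | 10% | 19% |
| 5 | 10% | 23% | 41% |
| 10 | 18% | 40% | 65% |

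For example, 1 − 0.95^5 = 0.226 and 1 − 0.90^5 = 0.410. Neither *u* nor *p* comes from the article. Each entry is the chance that an event occurs. It equals the chance of missing one only if nobody, including the therapist, ever learns of it. The width of the range, 4% to 65%, shows that the document does not determine the size.

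**The case against.** The strongest case on the other side has five parts.

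- **Everyone is tied to medical staff.** Diagnosis by hospital doctors applies to advertisement recruits as well, and psychiatrists run the weekly sessions. This stands. A reader might infer that some participants have no stated source at all, or that some definite share of the sample is uncovered. The article does not support either. What the link does not ensure is that staff learn of an arrest or an outside admission.
- **The list is not exclusive.** The sentence names sources without ruling others out, so reading it as only these is an inference. This stands too. The contrast with the participant interview, which is confined to subjective effects, still makes it the natural reading of the plan as written.
- **A contact person is presupposed.** The wording implies that participants have one, and registering a contact may be left to the full protocol or the consent form, neither of which is shown. Its absence from the entry criteria is therefore no finding.
- **Concealment matters less than it seems.** A contact can report an admission, an arrest or a death without knowing about the gambling. This largely stands, so the point does not rest on secrecy within families.
- **Therapists contact absentees.** They may well learn why someone stopped. This is a real route during treatment, and it rules out asserting that arrests or admissions would be logged as simple non-attendance. But event inquiry is not its stated purpose, and no such contact is described after week 10.

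**Conclusion.** The concern holds in limited form. Followed as written, the plan names third parties for hospitalization, arrest and death, asks the participant once about subjective effects, and states no harms inquiry at T3. Under-ascertainment is plausible, chiefly for arrests, for events between weeks 10 and 16, and for events in non-attenders.

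Its size is unknown. The table above illustrates a range under assumed inputs, and no single value in it should be quoted as an estimate.

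A reader might go further and infer that harms will be counted well in hospital patients and poorly in advertisement recruits. That is conjecture: the article gives no split by recruitment route, plans no comparison of harms between routes, and requires the hospital diagnosis of both groups.

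The conclusion assumes that the full protocol, which is not shown, does not already ask participants about these events. It calls for a low-cost improvement to harm ascertainment and does not put the design in doubt.

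**What to change.** In Data monitoring:

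1. Keep the third-party sources. They are needed for death and for participants who cannot be reached.
2. Add the participant as a direct source for hospitalization and arrest, asked at T2, at T3 and whenever a therapist contacts someone who missed a session. Each question should cover the time since the last inquiry.
3. Record at enrolment whether a contact person has been named. Do not make this a condition of entry: it could exclude the secretive or stigmatised gamblers whom online delivery is meant to reach.
4. Report how many of the 20 participants had event status ascertained through T3, so that a count of zero events can be told apart from an absence of information.

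The cost is one or two extra questions at contacts already planned. Some participants will be reluctant to report an arrest, so self-report adds to the third-party sources and does not replace them. The article states that recruitment had not begun at submission, so on that footing the change could apply from the first participant.
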